## Abstract

**Introduction:**

Trauma can play an important role in the development of psychosis, yet no studies have investigated whether a trauma-focused psychological therapy could prevent the onset of psychosis in people at high risk of developing this condition. This study aims to establish whether it would be feasible to conduct a multicentre randomised controlled trial (RCT) to investigate the clinical and cost-effectiveness of eye movement desensitisation and reprocessing (EMDR) therapy to prevent the onset of psychosis in people with an at-risk mental state (ARMS).

**Methods/analysis:**

This is a single-arm trial with a nested qualitative study where all participants (target n=20) will be offered EMDR. Eligible participants are those who meet criteria for ARMS; have experienced a traumatic event before the onset of ARMS symptomatology; and have at least one symptom of post-traumatic stress disorder (PTSD). Participants will be followed up at 4, 8 and 12 months after the baseline assessment. The primary outcome measure is transition to psychosis, and secondary outcome measures include severity of psychotic symptoms, PTSD, depression, anxiety, impaired functioning, health status and resource use. The analysis will aim to establish the rates of recruitment and retention for a large-scale RCT. Interviews with therapists and patients will explore their views of the study and their experiences of delivering or receiving EMDR.

**Ethics and dissemination:**

This protocol has been approved by the South West-Cornwall and Plymouth Research Ethics Committee (Reference 18/SW/0037). Findings will be disseminated through journal publications, conference presentations and meetings with service users, their families, mental health professionals and commissioners.

**Trial registration number:**

ISRCTN31976295.

Strengths and limitations of this studyThis is the first study to investigate the feasibility of conducting a large multicentre randomised controlled trial (RCT) of eye movement desensitisation and reprocessing (EMDR) for the prevention of psychosis in people with at-risk mental state.The study includes qualitative work to explore therapists and patients’ views of the treatment offered/received.Therapy sessions follow an EMDR protocol specifically designed for people with psychosis.The decision to change the study design to a single-arm trial may limit our ability to draw robust conclusions about recruiting to an RCT.

## Introduction

Psychotic illnesses are one of the leading causes of disability worldwide.^1^ The onset of psychosis is often preceded by a prodromal phase, known as an at-risk mental state (ARMS) for psychosis, which is characterised by a series of non-specific or attenuated psychotic symptoms.^2^ Approximately 22% of ARMS individuals will transition to psychosis within 1 year and 36% of them within 3 years.^3^

Various interventions have been used for the prevention of psychosis, but there is still limited evidence on the effectiveness of these approaches. Clinical guidelines recommend cognitive–behavioural therapy (CBT) as a first-line treatment.^4^ However, while a meta-analysis of randomised controlled trials (RCT) showed that CBT has a moderate effect on transition to psychosis at 12 months of follow-up (relative risk (RR) 0.64, 95% CI 0.44 to 0.93), the evidence was of low to moderate quality and the effect was not maintained over the longer term (18 months: RR 0.55, 95% CI 0.25 to 1.19).^5^

Exposure to trauma is two to three times more common in ARMS or psychosis than in controls,^6–8^ and post-traumatic stress disorder (PTSD) is also common, although not usually detected.^9^ Despite strong evidence showing that trauma is a key factor in the development of psychosis,^10–12^ no studies have yet investigated whether a trauma-focused therapy could prevent the onset of psychosis in ARMS.

Eye movement desensitisation and reprocessing (EMDR) is a trauma-focused therapy that has comparable efficacy to trauma-focused CBT (TF-CBT) in treating PTSD.^13–16^ However, the two forms of therapy are different. While TF-CBT seeks to directly identify and restructure the negative beliefs, EMDR does this indirectly, relying more on the integration of emotional, cognitive, sensory, physical and contextual information to allow adaptive processing of traumatic memories. Unlike TF-CBT, EMDR does not require patients to give a detailed description of the trauma, which may be distressing. Also, unlike TF-CBT, EMDR does not involve homework, which may make it more suitable for people with a disorganised lifestyle, such as those with ARMS.

To date, there has been only one RCT comparing EMDR with treatment as usual (TAU) in patients with comorbid psychosis and PTSD. This study showed that EMDR improved PTSD, and also reduced paranoid delusions, but did not reduce auditory hallucinations at 6 months of follow-up.^17^ However, the EMDR protocol did not specifically target psychotic symptoms. Furthermore, most participants had chronic forms of psychosis and hence psychotic symptoms might have been less amenable to treatment than more recent onset symptoms present in ARMS subjects.

### Objectives

The overarching aim of this study is to establish whether it would be feasible to conduct a large multicentre RCT to evaluate the clinical and cost-effectiveness of EMDR to prevent the onset of psychosis in people with an ARMS. The study has the following objectives:

To estimate the rate of recruitment and retention to inform the large-scale RCT.To refine the eligibility criteria, screening and recruitment procedures.To optimise the EMDR protocols and learn about the factors which affect the implementation of EMDR.To explore patients and therapists’ views of EMDR as a treatment for ARMS.To investigate patients and therapists’ views of the study design and study materials.To understand what TAU consists of for patients with ARMS.

## Methods and analysis

### Study design

The study consists of a single-arm feasibility trial with a nested qualitative study, and is conducted in collaboration with the Early Intervention (EI) teams from the Avon and Wiltshire Mental Health Partnership NHS Trust (AWP). All participants will be offered EMDR, and will be assessed at baseline, 4, 8 and 12 months of follow-up as described below.

The study design outlined is the final version of the trial protocol. The original protocol was changed as a result of low recruitment. Recruitment challenges are described later.

### Inclusion and exclusion criteria

#### Inclusion criteria

Aged 16 years or over who are at risk of psychosis (as defined in the Comprehensive Assessment of At-Risk Mental States (CAARMS)).^2^Presence of at least one positive symptom of psychosis (perceptual abnormality, unusual thought content, non-bizarre ideas or disorganised speech) scored ≥3 on CAARMS.History of traumatic experience as defined in International Classification of Diseases 10th Revision (ICD-10) F43.1, occurring prior to onset of first positive symptom.Presence of one or more symptoms of reliving, avoidance, hyperarousal or cognitive distortions in relation to the traumatic experience (assessed using the PTSD Checklist for DSM-5 (PCL-5)) during the last month.^18^

#### Exclusion criteria

History of treated or untreated psychotic illness or learning disability.Currently taking antipsychotics.Currently receiving psychological therapy.Completed a trauma-focused psychological therapy in the last 2 years.Insufficient fluency in English.Lacking mental capacity to provide valid informed consent.

### Recruitment procedure

Participants will be identified via two routes.

#### EI services

Researchers will identify clinical teams who are willing to identify potential participants via the following routes:

During routine clinic appointments—clinicians will introduce the study to patients who have met ARMS criteria within the past 12 months. Interested patients will be asked to complete section 1 of an Expression of Interest (EOI) form, and to provide their contact details. Completed EOI forms will be returned to the research team by secure email. A member of the research team will telephone interested individuals and, if the individual is willing to take part, agree a time and place for the researcher to meet with them to complete the eligibility assessment. Following the telephone call, the researcher will post the individual a full participant information sheet and a letter confirming the appointment.Individuals who do not want to hear more about the study will be asked to complete section 2 of the EOI form, which asks for information on age, gender, reasons for non-participation and willingness to take part in a short interview (see ‘qualitative data collection’ for more details).Postal or telephone invitations from clinicians—if clinicians do not introduce the study to patients during the appointment, they will post patients with ARMS a brief information sheet about the study, an EOI form and a stamped addressed envelope. Clinicians may also introduce the study to patients over the telephone. If the patients are interested, the clinician will ask the patients for permission to share their contact details with the research team. The clinician will then fill in the ‘Phone permission to contact’ form and will email it to the research team. Recruitment will then proceed as outlined in (A).Postal invitations sent out by National Institute for Health Research (NIHR) Clinical Research Network Clinical Studies Officers (CSO)—CSOs will prescreen potential participants using the electronic patient record system (RiO), and liaise with the care team regarding potentially eligible patients who will then be sent a brief information sheet and details on how to contact the research team if they are interested in the study. Patients who do not reply will be followed up by telephone by the CSO within a week of receiving the documents. If the patient is interested in the study, the CSO will take permission over the phone to share their contact details with the research team. Once the research team have received contact details, recruitment will proceed as outlined in (A).

#### Everyone included within AWP

‘Everyone Included’ is a standard approach to research in AWP, whereby service users are routinely informed about relevant research opportunities. The AWP Research and Development department will send a ‘Research Opportunity Letter’ on behalf of the research team to potential participants briefly explaining the study and what it involves. A researcher will telephone individuals who are interested in the study and answer any questions. If the individual is willing to take part, an eligibility assessment will be arranged.

### Consent and baseline eligibility assessment

Individuals interested in taking part will be invited to a face-to-face appointment with a researcher to establish eligibility, answer questions about participation and obtain written informed consent.

The process of consenting young people (16 and 17 years old) will follow the Department of Health Reference Guide to Consent^19^ and the Good Medical Practice Guidelines,^20^ which provide the guide that all health professionals need to take into account in obtaining consent. Although young people may be more vulnerable than adults, they are presumed to be able to give consent to their treatment. As in the case of adults, if young people decline to take part in the study their decision will be fully respected and accepted.

In order to establish eligibility, patients will be asked to complete the following scales:

Life Events Checklist for DSM-5.^21^Childhood Trauma Questionnaire.^22^PCL-5.^18^

Those who are eligible will be asked to provide written informed consent for their participation in the trial and sociodemographic information. Additional baseline data will be collected using the following quantitative measures:

Severity of psychotic symptoms: CAARMS,^2^ the Negative Scale of the Positive and Negative Syndrome Scale (PANSS),^23^ the Psychotic Symptom Rating Scales (PSYRATS)^24^ and the Community Assessment of Psychic Experiences (CAPE-42).^25^Severity of depression and anxiety: Patient Health Questionnaire (PHQ-9) for depression^26^ and Generalized Anxiety Disorder Questionnaire (GAD-7) for anxiety.^27^Impaired functioning: Work and Social Adjustment Scale (WSAS).^28^Health status: Five-Level version of the EQ-5D (EQ-5D-5L).^29^Drug use: the Drug Abuse Screening Test (DAST-10).^30^

Data will also be collected on medication use via self-report measures. The baseline eligibility assessment will last about 90 min.

### Intervention: EMDR

Participants will receive up to 12 sessions of manualised, weekly, face-to-face EMDR therapy.^31^ Treatment has been manualised by EMDR consultants from Lancashire and South Cumbria Care NHS Foundation Trust (LSCFT) and individualised to target psychotic symptoms. The treatment protocol was developed and evaluated through pilot cases with first-episode psychosis clients,^32^ and further refined as part of an ongoing feasibility RCT funded by the NIHR (PB-PG-0317-20037; ISRCTN43816889). Therapeutic sessions will be delivered by EMDR UK and Europe trained therapists who will receive training based on the LSCFT manual for the study. The training will be tailored to therapists’ needs, and will last between 4 and 8 hours. All EMDR therapists will have at least 1 year of experience of providing EMDR, and monthly supervision with an EMDR consultant will be in place. Each session will last approximately 90 min. The first two to four sessions will focus on establishing the therapeutic alliance, preparation for EMDR and stabilisation techniques, assessment and identification of targets, cognitions, emotions and bodily sensations. The following 8–10 sessions will focus on desensitisation, installation of positive cognitions and body scan for past, present and future stressful situations.

Written permission will be sought to audio record the therapeutic sessions. Ten per cent of the sessions will be randomly sampled and evaluated by accredited EMDR therapists independent of the study, to check treatment fidelity, using the EMDR fidelity checklist.^33^ Therapists will be encouraged to liaise with participants’ care coordinators as this could improve participants’ adherence to therapy. If a serious adverse event (SAE) occurs in relation to therapy, or participant has difficulties engaging with therapy to the point where therapy is no longer worthwhile, the therapy will be discontinued.

### Challenges to recruitment

The original feasibility study was designed as an RCT comparing EMDR with TAU. TAU in AWP is quite heterogeneous and consists of discharge back to the referrer, signposting to other services, CBT, family intervention or psychoeducation. Randomisation took place using a remote computerised randomisation service administered by the Bristol Trials Centre ensuring that allocations were concealed from the recruiting researcher. Randomisation was minimised by psychotic symptom severity (score on positive symptoms on CAARMS <11 or ≥11). However, following challenges to recruitment (described below), the study design was changed to a single-arm study.

During the first 7 months of the study (May to December 2018), we only recruited three participants (against a target of 21). This poor recruitment was primarily because the number of patients identified as ARMS by the EI teams within AWP was much lower than expected, and only three of the six EI teams we originally planned to recruit from were able to support the study due to financial constraints to managing ARMS clients. Therefore, from July 2019, all participants recruited to the study were offered EMDR. Figure 1 shows the flow of participants in the randomised and single-arm phases of the trial.

**Figure 1 F1:**
[figure not shown]
Study flow chart for the feasibility trial (randomised and non-randomised components). EMDR, eye movement desensitisation and reprocessing; FU, follow-up; TAU, treatment as usual.

### Sample size and feasibility of recruitment

In the original protocol we had planned to recruit up to 40 participants. The initial sample size was informed by literature guidelines^34^ and pragmatic considerations concerning potential difficulties accessing this population. The feasibility study would not be powered to detect important clinical differences between EMDR and TAU groups but would provide estimates of the completion and retention rates that would further assist in planning the recruitment for a future RCT.

Given the challenges with recruitment and modification of our study design (from a randomised to single-arm trial), we decreased our target sample size from 40 to 20 participants. This sample size will provide us with reasonable precision around estimates of percentages completing the intervention and follow-ups. For example, if 70% of those who started EMDR complete the intervention, the 95% CIs would be 45% and 88%. Similarly, if 75% of those who started EMDR are followed up to 12 months, the 95% CIs for the retention rate would be 50% and 91%.

### Outcome assessment

The follow-up schedule will involve face-to-face assessments at 4, 8 and 12 months after the baseline assessment. Each follow-up assessment will last about 60 min. The primary outcome will be collected at 12 months of follow-up, and the secondary outcome at 4, 8 and 12 months.

A 12-month follow-up will provide us with adequate data on retention rate that can be used to ensure that a definitive trial is adequately powered. If, in the definitive trial, the intervention was shown to be effective at 12 months, then further follow-up could examine whether effects are maintained over the longer term.

### Primary outcome

Transition to psychosis: ICD-10 diagnosis of psychotic disorder from clinical records or via the CAARMS.

### Secondary outcome

Severity of psychotic symptoms: CAARMS, PSYRATS, the Negative Scale of the PANSS and CAPE-42.Severity of PTSD symptoms: PCL-5.Severity of depression and anxiety: PHQ-9 and GAD-7.Impaired functioning: WSAS.Health status: EQ-5D-5L.Drug use: DAST-10.Medication use.Resource data use—we will ask questions about resource use including information on the use of primary and secondary care services, use of social services and disability payments received, time off school or work and productivity loss due to time off work or study.

If there are difficulties following up trial participants to obtain outcome data, researchers will prioritise collection of data on psychotic symptoms, PTSD symptoms and medication. Following the switch to single-arm design, it will no longer be possible to blind researchers to treatment allocation in terms of avoiding potential bias in outcome measurement.

### Quantitative data analysis

Quantitative data will be analysed in Stata V.15.^35^ If there are no differences in baseline characteristics of those who were randomised and those who enter the single-arm study, we will combine data to generate summary statistics on: (1) the proportion consenting to take part in the study; (2) the proportion completing the baseline assessment and agreeing to take part in the study; (3) the number of EMDR sessions attended and the proportion completing eight or more sessions (regarded as an adequate dose of therapy); (4) the proportion completing the follow-up assessments. Feasibility outcomes such as recruitment and retention rates will be calculated with 95% CIs using the exact binomial method.

We will also report the proportion of individuals who transitioned to psychosis at 12 months, and the CIs for the effect size will be calculated to assist the planning of a future RCT. We will also compare the continuous outcomes such as the severity of psychotic symptoms, depression, anxiety, PTSD symptoms and quality of life to show the frequency of data completion, mean and SD for the three time points.

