### Summary of changes to the original feasibility study

There have been a number of changes to the original feasibility study. These are summarised below:

Change of study design from randomised trial to single-arm trial.Decrease in sample size from 40 to 20 participants.Change in the measure used to assess the severity of psychotic symptoms at baseline and follow-up assessments from the Positive Scale of the PANSS to the CAARMS, as the latter is more sensitive.Extending the time between patients being identified as ARMS to the time when they can be recruited into the study from 3 to 12 months.Additional interviews with GPs, other clinicians from primary and secondary care services, patients with ARMS and researchers to better understand identification and management of patients with ARMS, including routes into primary and secondary services.

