### Feasibility trial status

Recruitment to this study opened in May 2018, and closed in May 2020. At the time of writing (July 2020), 14 participants have been recruited to the study. We expect to finish follow-up data collection by May 2021.

This article describes protocol version 4, dated 2 August 2019. When all regulatory approvals had been received, the protocol was version 1, dated 11 January 2018. Since then, two major amendments have been made with changes to incorporate additional qualitative work, decrease the sample size and change the study design from an RCT to a single-arm trial. The latter change took place in July 2019 prior to which we had recruited six participants.

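### The condition for pooling the randomised and single-arm phases is uninformative at 6 v 8 participants and does not bear on consent or follow-up, so the pooled proportions may not estimate the rates an RCT needs

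*Protocol article*

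**What the plan says.** The rule is in the protocol article under Quantitative data analysis: "If there are no differences in baseline characteristics of those who were randomised and those who enter the single-arm study, we will combine data". Four summaries follow. They include "the proportion consenting to take part in the study" and "the proportion completing the follow-up assessments"; the other two are baseline completion with agreement to take part, and EMDR sessions attended with the proportion reaching eight or more. The section adds: "Feasibility outcomes such as recruitment and retention rates will be calculated with 95% CIs using the exact binomial method". It gives no list of characteristics, no tolerance and no method for judging the condition.

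The first item under Objectives is to estimate recruitment and retention for the large RCT.

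Under Challenges to recruitment, the study began as a randomised comparison of EMDR with TAU, and "from July 2019, all participants recruited to the study were offered EMDR". Feasibility trial status gives the counts: "The latter change took place in July 2019 prior to which we had recruited six participants", and 14 in total by July 2020, after recruitment had closed in May 2020.

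The strengths and limitations box concedes that the switch to a single arm "may limit our ability to draw robust conclusions about recruiting to an RCT".

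**The concern.** There are two separate problems.

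First, the condition cannot do its job at this size. If two groups of 6 and 8 look alike, large differences between them remain possible. If they look different, that may be chance. With no tolerance stated, whether the phases are pooled is left close to arbitrary.

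Second, even a perfect baseline match would not answer the question. Baseline characteristics are measured on people who joined. The proportion consenting depends equally on those who declined, and they are not in the comparison. The earlier group agreed to a chance of TAU and the later group to assured EMDR. Follow-up raises a similar question: the randomised group includes anyone allocated to TAU, which according to the article could mean discharge back to the referrer, so equal retention should not be presumed.

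At stake is the first objective. A single blended proportion could be carried into RCT planning although it describes neither consent to randomisation nor follow-up in a two-arm trial.

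**Working it through.** **Inputs**
- Recruited before the switch: 6 (Feasibility trial status), taken as all randomised (assumption).
- Total recruited: 14 (same section), so single-arm = 14 − 6 = 8.
- Target: 20 (Sample size and feasibility of recruitment). If the six count towards it (assumption), the split would have been 6 v 14.
- Interval method: exact binomial (Quantitative data analysis).
- The article states no figure for the pooling rule, and no consent or retention rate by phase.

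**1. The plan's own precision figures.** Exact binomial intervals at n = 20:
- 70% = 14/20: 45.7% to 88.1% (stated 45% and 88%).
- 75% = 15/20: 50.9% to 91.3% (stated 50% and 91%).

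Both agree when cut to whole per cents, so the method is confirmed. In the article these intervals refer to people who started EMDR, which is not the same set as everyone randomised plus everyone in the single-arm phase.

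**2. What a baseline comparison can show.** The 95% half-width for a mean difference, in SD units, is t(0.975, n1+n2−2) × √(1/n1 + 1/n2).
- 6 v 8: 2.179 × √(1/6 + 1/8) = 2.179 × 0.540 = 1.18 SD.
- 6 v 14: 2.101 × √(1/6 + 1/14) = 2.101 × 0.488 = 1.03 SD.

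An observed difference of exactly zero would therefore still be compatible with a true difference of more than 1 SD either way.

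**3. If a two-sided 5% t-test were used** (an assumption; the article names none). Power from the noncentral t distribution, with noncentrality d/√(1/n1 + 1/n2):

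| True difference | 6 v 8 | 6 v 14 |
|---|---|---|
| 0.5 SD | 14% | 16% |
| 0.8 SD | 28% | 34% |
| 1.0 SD | 40% | 49% |
| 1.5 SD | 72% | 83% |

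Power of 80% needs about 1.65 SD (6 v 8) or 1.45 SD (6 v 14).

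**4. What pooling could do.** All rates here are assumed, for illustration only. Pooled retention = (6 × randomised rate + 8 × single-arm rate)/14.
- 50% v 80%: (3.0 + 6.4)/14 = 67%, which is 17 points above the randomised-phase rate.
- 70% v 80%: (4.2 + 6.4)/14 = 76%, 6 points above.
- 75% v 75%: 75%, no difference.

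For consent, people approached = recruits/consent rate. At 30% v 60%: 14/(6/0.3 + 8/0.6) = 14/(20 + 13.3) = 42%, against 30% for consent to randomisation. At 50% v 50% there is no difference.

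**5. Cost of separating the phases.** If 4 of 6 randomised participants were followed up (illustrative), the exact interval is 22% to 96%.

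**The case against.** The strongest reply is that this is descriptive feasibility work in 14 people. Thresholds for comparability may sit in a fuller document, the limitation on RCT recruitment is openly stated, the article's flow chart is said to show both phases, and interviews with decliners, clinicians and other researchers address recruitment directly. All of this is true and lowers the consequence. It does not repair the rule: a better-defined baseline threshold would still say nothing about whether consent to randomisation equals consent to assured EMDR.

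Several stronger readings are tempting, and the article does not support them.
- *That pooling hangs on an underpowered significance test.* No test, significance level or variable list is given, so the power figures above are conditional. Power is also not negligible for very large differences.
- *That the estimates are bound to be biased.* Bias needs consent or retention to differ by phase, and no phase-specific figures are given.
- *That monthly accrual proves a phase effect.* On the stated dates, 6 in about 14 months against 8 in about 10 is a rate ratio of (8/10)/(6/14) = 1.87, exact 95% interval 0.57 to 6.5, p = 0.28. Recruits per month is not among the pooled items, and the article attributes early low recruitment mainly to few identified patients and few participating teams.
- *That TAU participants enter the EMDR attendance denominator.* The item naturally concerns those offered EMDR, and the sample-size section uses those who started EMDR. The allocation split of the six is not given in the text.
- *That transition to psychosis is pooled under this rule.* It is in a separate paragraph with no such condition.
- *That the eligibility window separates the phases.* The summary of changes lists "Extending the time between patients being identified as ARMS to the time when they can be recruited into the study from 3 to 12 months" but does not date it.

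**Conclusion.** The concern holds in a limited form. The condition is undefined, and at 6 v 8 it is uninformative (half-width 1.18 SD; 28% power at 0.8 SD if a 5% t-test were used). More importantly, it is the wrong criterion for consent at any sample size, and it leaves any TAU participants inside the pooled follow-up proportion. The pooled consent and follow-up figures may therefore not estimate what the first objective needs. The size and direction of any error cannot be known from the article: the assumed 6 v 8 retention scenarios run from 0 to 17 points. EMDR attendance is affected least.

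This rests on the six early recruits all having been randomised and on the illustrative rates. It should be corrected before analysis, but it does not undermine the study.

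**What to change.** Delete the baseline condition from the Quantitative data analysis section and state, whatever the baseline comparison shows:
- consent and baseline completion are reported by phase;
- follow-up completion is reported by phase, and by arm within the randomised phase;
- sessions attended and the proportion completing eight or more are reported for everyone offered EMDR, meaning those randomised to EMDR plus the single-arm participants;
- any figure pooled across phases is labelled secondary;
- baseline characteristics are described by phase, without testing.

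This changes analysis wording only and needs no new data. The cost is wide intervals for the phase-specific proportions, which is the true precision of the evidence on a randomised design.

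### The listed recruitment statistics are proportions with exact binomial intervals, so none estimates enrolment per month or per team, which is what an RCT plan needs

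*Protocol article*

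**What the plan says.** The first item under Objectives in the protocol article is "To estimate the rate of recruitment and retention to inform the large-scale RCT".

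Quantitative data analysis lists four summaries. Two concern entry to the study: one is "the proportion consenting to take part in the study", and the other is the fraction who finish the baseline visit and agree to join. The third concerns therapy received, "the number of EMDR sessions attended and the proportion completing eight or more sessions", and the last is the fraction assessed at follow-up.

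The section also assigns the interval method: "Feasibility outcomes such as recruitment and retention rates will be calculated with 95% CIs using the exact binomial method". It does not define the recruitment rate or give a denominator for the consent proportion.

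Sample size and feasibility of recruitment illustrates precision for two proportions only: 70% completing therapy (45% to 88%) and 75% followed to 12 months (50% to 91%).

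Challenges to recruitment describes recruitment as a count over time. In the first 7 months, "we only recruited three participants (against a target of 21" planned for that period. The stated causes are fewer ARMS patients identified than expected and only three of six early intervention teams able to support the study.

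**The concern.** The number of sites and the length of a future RCT follow from how many people one team enrols in a month. Every recruitment summary listed is a fraction of people at some stage of the pathway, and the only interval named for recruitment is one for fractions. The reasons given for the shortfall, patient supply and team participation, act before anyone is asked to consent. A consent proportion could therefore look the same in a study that recruits quickly and in one that recruits too slowly to be feasible.

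Slow recruitment is also what led this study to drop randomisation and halve its target from 40 to 20. The listed analysis would give no estimate or interval for it.

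**Working it through.** **Reproducing the article's intervals.** Clopper-Pearson limits are the 2.5% quantile of Beta(x, n−x+1) and the 97.5% quantile of Beta(x+1, n−x). With n = 20:

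- 14/20 = 70%: 45.7% to 88.1% (article: 45% and 88%)
- 15/20 = 75%: 50.9% to 91.3% (article: 50% and 91%)

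Both agree within one percentage point. The exact binomial is the method used, and it suits these proportions.

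**What a consent proportion can show.** The number approached is not given, so it is assumed here. With 14 enrolled:

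- 20 approached: 70% (46% to 88%)
- 28 approached: 50% (31% to 69%)
- 40 approached: 35% (21% to 52%)
- 70 approached: 20% (11% to 31%)

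Each result is the same whether enrolment took 7 months in six teams or 24 months in three.

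**The rate over time.** Inputs from Feasibility trial status: recruitment ran from May 2018 to May 2020 (about 24 months); 14 were recruited in total; 6 of them before the July 2019 switch (about 14 months). That leaves 14 − 6 = 8 in about 24 − 14 = 10 months. Inputs from Challenges to recruitment: 3 recruited, against 21 planned, in 7 months.

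For x enrolled in T months the rate is x/T. The exact Poisson limits are χ²(0.025; 2x)/(2T) and χ²(0.975; 2x+2)/(2T).

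| Period | x / T | Per month | 95% CI |
|---|---|---|---|
| First 7 months | 3 / 7 | 0.43 | 0.09 to 1.25 |
| Before the switch | 6 / 14 | 0.43 | 0.16 to 0.93 |
| Single-arm phase | 8 / 10 | 0.80 | 0.35 to 1.58 |
| Overall | 14 / 24 | 0.58 | 0.32 to 0.98 |
| Planned, first 7 months | 21 / 7 | 3.0 | – |

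The planned rate lies above every upper limit.

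**Sensitivity to the dates.** Only calendar months are given. Counting May to December 2018 as 8 months gives 3/8 = 0.38 (0.08 to 1.10). Counting the single-arm phase as 11 months gives 0.73 (0.31 to 1.43), and the whole period as 25 months gives 0.56 (0.31 to 0.94). The picture does not change.

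**Per team.** The number of teams open in each month is not given. Overall:

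- three teams throughout: 0.583/3 = 0.19 per team-month (0.11 to 0.33)
- six teams throughout: 0.583/6 = 0.10 per team-month (0.05 to 0.16)

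If the plan assumed six teams, it implied 3.0/6 = 0.50 per team-month.

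**The case against.** The strongest reply is that nothing is misapplied. The Sample size section uses retention rate for a percentage followed up. If recruitment rate likewise means the first or second listed proportion, the exact binomial is the right interval. That stands. A reader might infer that the article puts a binomial interval on a monthly rate, but it never proposes a monthly rate. The gap is that the rate is undefined and no time-based estimate is listed.

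Second, this is a condensed article, its list of feasibility outcomes is introduced as examples, and a full protocol or analysis plan may define the rate. That is possible. But the article does name a method for the recruitment rate, and the method it names fits only a proportion.

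Third, recruitment problems are examined elsewhere: the added qualitative work covers how ARMS patients are identified and referred, and other researchers' experience of recruiting them. That work helps explain the shortfall, but it produces no rate.

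Some stronger readings are tempting and should not be drawn:

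- That the consent proportion will be close to 100%, because "Those who are eligible will be asked to provide written informed consent for their participation in the trial" places consent after an expression of interest, a telephone call and a face-to-face visit. The analysis section gives no denominator, and the expression-of-interest form also records people who decline earlier.
- That Objective 1 cannot be met. A monthly rate can be computed from figures already in the article, as above.
- That the results convert to a firm number of team-months for the RCT. Open teams per month are unknown, the intervals are wide, and an RCT sample size would have to borrow an effect from another therapy.

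**Conclusion.** The point holds as a gap in the listed analysis, not as an invalid interval. The recruitment objective exists to inform an RCT, the article judges its own recruitment per unit of time, and none of the listed summaries gives that quantity or its uncertainty. Overall enrolment was about 0.58 per month (0.32 to 0.98), roughly a fifth of the planned 3.0 (0.58/3.0 = 0.19).

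The monthly figures rest on approximate calendar months and on a constant rate within each period, which the Poisson interval assumes. The per-team figures rest further on an assumed three to six open teams and are illustrative only. The intervals for the two phases overlap widely, so the higher point estimate after the switch is not evidence that dropping randomisation improved recruitment. The change is worth making because it supplies the missing planning quantity at almost no cost.

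**What to change.** In Quantitative data analysis:

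- Define the recruitment rate as participants enrolled per month, reported separately for the randomised and single-arm phases and overall, with an exact Poisson 95% CI.
- Where team opening dates are available, also report enrolment per open early intervention team per month. The article does not say whether these dates were recorded, so this part is conditional.
- Keep the exact binomial for consent, therapy completion and follow-up, and state the denominator of each proportion.

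The cost is a change of analysis wording and some extra tabulation. The monthly rates need only the counts and dates the article already reports. With 14 recruits the intervals will be wide, and the report should say so.
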